### *Reliability and Validity Checks*

As mentioned above, in part in order to improve replicability (and thus reliability) of this study, a session content checklist will be used during the sling intervention session, so that the same intervention may be given both across participants and across studies should future

studies utilise this checklist.

In order to support the replicability and validity of this study, a CONSORT flow diagram (Moher, Schulz, & Altman, 2001) will be included in the reporting of the study (please see Appendix W).

This study aims to use only measures that have been validated and found to be reliable by past studies. Both intervention and control participants will be recruited from the same population. The intervention used in this study is representative of the intervention that a parent may typically receive from the service in which the study takes place (the sling surgery). Furthermore the study will take place in the usual setting, and with the usual staff, that such an intervention would normally involve.

### *Ethical Implications*

Ethical approval will be sought from the University of Sheffield. As mentioned in the *Procedure* section above, during recruitment, participants will be given information explaining the aims and procedure of the study (please see Appendix Q). They will be asked to complete a consent form prior to participating in the study (Appendix R). It will be made clear that participants are free to withdraw their data at any time. Participants will also be debriefed at the end of the study (Appendix V).

As mentioned in the *Primary Measures* section above, during the study, it may be that participants score above the clinical threshold applied in NHS settings on the EPDS. Should this happen, participants will be sent a letter (please see Appendix E) recommending that they speak to their midwife or health visitor, and also their GP. The letter will be marked “Private and Confidential”.

It must be acknowledged that there is an incentive for participation in this study, in that participants in both conditions will receive sling hire and training for free, that they might have otherwise paid for. Furthermore, while control participants will receive the intervention (sling hire, training and support) following completion of the study, they will receive one month of free sling hire, support and training, the intervention participants will have received three months of free sling hire, support and training over the course of the study. While this discrepancy may appear unfair, it is commensurate with sling library advice and based on the different level of support needed in relation to infant age. Parents of very young infants usually require more support with sling use than parents of older infants.

### **Timetable/ Plan of work**

Following application for ethical approval in December 2018, it is hoped that recruitment will begin in February 2019.

Baseline measures (T1) will be collected from participants in both conditions, between late February 2019 and late July 2019. The aim will therefore be, to recruit participants whose due date falls within this period. Participants in the intervention condition will attend their session at the sling surgery during this period, once they have completed their baseline measures.

Following this, participants will complete T2 measures between April 2019 and mid-September 2019, and T3 measures between mid-May 2019 and late October 2019.

Following completion of data collection (from mid-May onwards, dependent upon when the participant completed their baseline measures), control participants will be offered one month's free sling hire, a session at the sling surgery and access to other support at the sling surgery.

It is hoped that data analysis may be completed by December 2019, ready for the results to be written up and submitted by May 2020.

This timetable is displayed in a Gantt chart in Appendix X.

### **Justification for Proposed Costs**

Proposed costs of the study are detailed in Appendix Y. These costs are for the printing of flyers for recruitment, and the printing of any letters to participants, should they score highly on the EPDS (see "Ethical Implications" section above). Included in the cost is a pay-as-you-go sim card, in order to communicate with participants via text if this is their preference.

In order to reduce costs, the majority of communication with participants (participant information, consent forms, sling surgery information) and the administration of measures, will be done electronically.

## Appendix A Recruitment Materials

### A.1: Recruitment Poster.

[Logos removed]

## Participants Needed - Free Sling Hire!

We are seeking  
volunteers for a  
maternal mental health  
and wellbeing  
research project.

[Images removed]

We are looking for women  
who are due to give birth  
between March 2019 and  
July 2019, and who have not  
used a baby sling before.

We want to see if using a sling might influence your mood, your  
general wellbeing, or your parenting experiences.

If you agree to participate:

- When your child is born, we would ask you to complete a set of online questionnaires 3 times over the course of 12 weeks.
- We would need you to travel to the Sheffield Sling Surgery for a one-off session where you will learn how to safely use a sling and be given a sling to hire for free for the duration of the study.
- You would be randomly assigned to one of two groups. For one group you will be asked to attend this session when your child is between 0 and 6 weeks old. If you are in the other group you will be asked to attend when your child is between 12 and 18 weeks old.

If you or anyone you know might be  
interested in participating, to learn more about it please email  
[name] (Trainee Clinical Psychologist and Principal  
Investigator) at:  
[[contact]](mailto:[contact])  
Contacting us in no way commits you to  
participate. And if you do agree to take part in this study, you can stop  
participating at any time.

This study has been approved by the University of Sheffield's Ethics Committee, reference 024147.

## Appendix B Items for All Time Points

### Sling Use Measure

#### **Sling Use and Access to Sling Surgery Services**

Over the past 6 weeks, how often would you say that you have used your sling?

- ☐ Not at all
- ☐ Once or twice
- ☐ A few times
- ☐ About once a day
- ☐ About twice or three times a day
- ☐ More than three times a day

Over the past 6 weeks, how often would you say that you have used a pram or buggy (or similar)?

- ☐ Not at all
- ☐ Once or twice
- ☐ A few times
- ☐ About once a day
- ☐ About twice or three times a day
- ☐ More than three times a day

Over the past 6 weeks, how often would you say that you have accessed the sling surgery services (either online, in person, or other)?

- ☐ Not at all
- ☐ About once a week
- ☐ About twice a week
- ☐ Generally more than three times a week
- ☐ Daily

You will be now be asked the same questions again, but about your partner:

Over the past 6 weeks, how often would you say that your partner has used the sling?

- ☐ Not at all
- ☐ Once or twice
- ☐ A few times
- ☐ About once a day
- ☐ About twice or three times a day
- ☐ More than three times a day
- ☐ N/A

Over the past 6 weeks, how often would you say that your partner has used a pram or buggy (or similar)?

- ☐ Not at all

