## Measures

All measures are self-report and will be completed online using the programme

Qualtrics.

At this stage in the research process a number of measures have been selected to be administered to participants. As mentioned in the “Service User Involvement” section above, it is hoped that service users might feedback on whether, as it stands, this battery of measures is currently too onerous for participants to complete, particularly as baseline measures are due to be completed soon after childbirth. Thus while the full battery of possible measures is presented here, some of these measures may be omitted from the final battery administered to participants, based on service user feedback as well as the judgement of the researchers and staff at the sling surgery.

Primary Measures

*Sling Use and Support*

With the support of the sling surgery, as in previous studies (Anisfeld et al., 1990), an idiographic measure has been designed, asking participants how often they have used their sling over the past 6 weeks (please see Appendix B).

For comparison, participants will also be asked how often they have used a pram or stroller over the same time period.

This measure also asks participants how often they have accessed the services of the Sling Surgery over the past 6 weeks, or any other sling-related support.

Participants will be asked how often their partner has used a sling, pram, or accessed the Sling Surgery Services over the past 6 weeks, so that this information may be taken into account. This is partly in order to account for partner sling use as a possible confounding variable when analysing the results of the study, but it also acts as a way of capturing paternal involvement and use of slings, which may be of interest in future research.

At T2 and T3, participants will be asked whether they have swapped their sling over the past 6 weeks (the course of the study since the previous data collection time-point), and if so, how often they have done so.

The time period which all of the above questions refer to (6 weeks) may be altered according to feedback from the Sling Surgery and service users.

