### *Data Collection*

When their infant is 0 to 6 weeks old participants will complete baseline measures. For intervention participants completion of baseline measures will be prior to attending the sling surgery session. Currently these are due to include measures of PND (EPDS, DASS21), attachment (ECR-S), a measure of sling and buggy use and also of use of sling surgery services, a breastfeeding measure, and measures of wellbeing (WEMWBS/SWEMWBS), parenting (PSCS, CEQ), infant temperament (IBQ-R VSF) perceived social support (SPS) and general demographics (as mentioned in the *participants* section above).

As part of this feasibility study, it would be helpful to examine how long is needed before an effect of sling use upon maternal mental health, wellbeing and parenting may be seen. This information could support future RCTs in deciding the duration of a sling use intervention condition. It was agreed that an additional time-point, midway through the study, may help to narrow down the point at which an effect of sling use may be seen. Thus, 6 weeks

after completion of baseline measures, both intervention and control participants will be asked (via text or email - see below) to complete Time-2 (T2) measures online. These T2 measures are not the full battery of measures. Rather, participants in both groups will be asked about current sling use and use of sling surgery services (including whether they have swapped their sling). The EPDS will also be administered a second time at this time-point.

A further 6 weeks later (T3) participants in both conditions will be asked (via text or email - see below) to complete for a second time the full battery of measures that had been given at baseline (T1) (excluding demographic measures).

A text or email reminder (depending on each participant's stated preferred method of contact) will be sent each time that the participant is due to complete their next battery of measures. This message will contain a link to these measures (via Qualtrics).

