### *Proposed Analysis*

As a feasibility study it is difficult to predict participant drop-out rate, and the impact that this may have on the results of the study. In order to control for drop-out, intention-to-treat (ITT) analysis will be used.

A mixed ANCOVA will be used to evaluate the relationship between sling provision and maternal mental health, wellbeing and parenting. This will include a comparison of both within-group pre- and post-intervention scores, and a between-group comparison of intervention vs. control group scores.

Attachment will be included as two covariates, as the measure of attachment used in this study produces two scores (*Avoidance* and *Anxiety*).

Thematic analysis will be used to evaluate the data collected from the two qualitative questions included at T3.

As a feasibility study, the impact of treatment fidelity on the results of the study is of interest. In order to examine this impact, it may be helpful to run the analysis again, this time excluding data from control participants who have used a sling, or accessed the sling surgery services over the course of the study. Similarly, it may be helpful to then re-run the analysis again, but this time excluding participants in the intervention condition who did not use their sling regularly. Through a similar process, it may be important to re-analyse the results of the study, investigating whether the frequency of participants' partners' sling use impacts upon these results.

It will be important to investigate whether the results of various demographic groups differ, in order to inform the inclusion or exclusion criteria of future RCTs. Frequencies and descriptive statistics derived from the demographic measures will be examined and presented. If possible, tests of difference will be conducted using this data, though this will of course depend upon the size of the demographic groups.

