#### S.9 Qualtrics End Information - T1 - Control Group

**Information to be presented on Qualtrics at the end of the T1 battery of measures for the control group only.**

Thank you for completing these questionnaires.

You will receive an email or text, depending on your preference, letting you know when you are due to complete your next set of questionnaires in 6 weeks' time. If you have not told us whether you prefer to communicate with us via email or text, please let us know by emailing the following:

[[contact]](mailto:[contact])

Thank you again for participating,

Best wishes,

[name],

University of Sheffield.

S.10 Qualtrics End Information - T2 - Intervention Group

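### The fixed six-week look-back on the sling and pram items reaches before birth at T1 and leaves time unasked at T2/T3 when a questionnaire is late or missed, so control sling use can be understated

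*Protocol*

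**What the plan says.** Appendix B of the protocol (its contents entry reads "Appendix B Items for All Time Points") asks "Over the past 6 weeks, how often would you say that you have used your sling", with parallel items for pram or buggy use, for access to the Sling Surgery and for the partner. The answer options for sling and pram use mix counts over the whole period (*Once or twice*, *A few times*) with daily frequencies (*About once a day* and upwards).

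The Data Collection section puts "a measure of sling and buggy use and also of use of sling surgery services" in the baseline battery and fixes its timing: "When their infant is 0 to 6 weeks old participants will complete baseline measures". T2 is due six weeks after T1. The closing page at T1 promises a message "letting you know when you are due to complete your next set of questionnaires in 6 weeks' time", and for the last round the protocol says "A further 6 weeks later (T3) participants in both conditions will be asked". In Measures, under Sling Use and Support, the six weeks are equated with "the course of the study since the previous data collection time-point", but this is written for the sling-swap item only. The same section says that the six-week period may change after feedback from the Sling Surgery and service users.

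The reminder template (Appendix S.5) asks for completion as soon as possible and sets no limit. Proposed Analysis contemplates a re-analysis "excluding data from control participants who have used a sling, or accessed the sling surgery services over the course of the study".

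**The concern.** Aims and Hypotheses names treatment fidelity, including independent sling use by controls, as a particular focus of the study. Slings bought or borrowed elsewhere are visible only through these self-report items. If the items do not ask about part of the follow-up, a control who used a sling in that part is classed as a non-user. The contamination estimate then comes out too low, and the re-analysis keeps a woman it was meant to leave out. With 25-30 women per arm, each misclassified control moves the contamination proportion by 1/30 = 3.3 to 1/25 = 4.0 percentage points.

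At T1 the problem is different. Part of the window lies in pregnancy, when there was no infant to carry, so the answer reflects the infant's age as well as the mother's behaviour.

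**Working it through.** **Inputs.** Look-back of 6 weeks (Appendix B); infant age at T1 of 0 to 6 weeks, and T2 and T3 at 6 and 12 weeks after T1 (Data Collection); no completion limit (Appendix S.5); session requested within about two weeks of T1 (Appendix S.7 and S.8) and while the infant is at most 6 weeks old (Intervention).

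**The planned schedule is consistent.** Take late February as 22-28 February and late July as 24-31 July 2019 for T1.
- Adding 6 weeks gives T2 from 5-11 April to 4-11 September.
- Adding 12 weeks gives T3 from 17-23 May to 16-23 October.

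This agrees with the Timetable section (April to mid-September; mid-May to late October). Window and planned interval are both 6 weeks, and two on-time windows cover 6 + 6 = 12 weeks.

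**T1.** Share of the window that falls within the infant's life = age/6.

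| Infant age (weeks) | 1 | 2 | 3 | 4 | 5 | 6 |
|---|---|---|---|---|---|---|
| Share | 17% | 33% | 50% | 67% | 83% | 100% |

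If ages were uniform over 0-6 weeks (an assumption), the mean would be 50%. A mother of a one-week-old with seven pram outings could honestly choose *A few times* (over six weeks) or *About once a day* (since birth). The window still contains the whole of the infant's life, so no use of a sling with this infant falls outside it.

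**Late T2 or T3.** For an answer d weeks late, the unasked share of that interval = d/(6 + d). The protocol gives no delay, so d is assumed.

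| d (weeks) | 1 | 2 | 3 |
|---|---|---|---|
| Share of that interval | 1/7 = 14% | 2/8 = 25% | 3/9 = 33% |
| Share of whole follow-up, if the other questionnaire comes 6 weeks after the previous one | 1/13 = 8% | 2/14 = 14% | 3/15 = 20% |

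**Skipped T2, T3 on time.** T3 looks back over weeks 6 to 12 only. Unasked: 6/12 = 50%, the first six weeks after baseline.

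**Intervention arm at T2, even on time.** Weeks with the sling inside the window = 6 minus the lag from T1 to the session. Lags of 0, 1 and 2 weeks leave 6, 5 and 4 weeks. At the extreme (T1 at birth, session at 6 weeks of age) none is left. Low reported use at T2 may therefore reflect late receipt of the sling, not low adherence.

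**The case against.** Much of the case on the other side stands.

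- A reader might infer that use rates are computed over the wrong denominator. The protocol defines no rate. The items are ordinal categories, and nothing in the plan divides an answer by 42 days.
- A reader might infer that the T1 window conceals contamination. It cannot, because a window longer than the infant's life includes all of it. What suffers is the baseline description, chiefly pram use, since women who have already used a sling are excluded at entry.
- A reader might infer that the T2 and T3 windows are wrong by design. They match the planned interval, and the gap arises only when a questionnaire is late or missed. Misclassification also requires a control whose sling use fell wholly in the gap.
- The six-week period is declared provisional, and nothing limits a revision to another fixed period.
- Under Data Security and Management, hire and other access to Sling Surgery services are recorded independently of recall, which backs up the service-access half of the exclusion. It does not capture slings obtained elsewhere.
- The fidelity re-analyses are worded tentatively, and the sample size and the intention-to-treat analysis are untouched.

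What survives is narrower. Nothing in the protocol protects the items against late or skipped completion, drop-out is admitted to be hard to predict, and no analysis rule can recover a period that was never asked about.

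**Conclusion.** The point holds as a minor one. At T1 the mismatch is certain for every infant under 6 weeks, and its effect is ambiguity in the baseline categories. At T2 and T3 the mismatch is a risk and not an error in the schedule: 14%, 25% or 33% of an interval for assumed delays of 1, 2 or 3 weeks, and half of the 12 weeks for a woman who skips T2 and answers T3 on time. The documents give no figure for delays or skipped questionnaires, so how many controls would be misclassified cannot be stated. The direction is clear: missed use can only lower the contamination estimate. The documents do not support the wider conclusion that the use and contamination data are invalid.

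**What to change.** 1. At T1, ask the sling and pram items (mother and partner) *Since your baby was born*. The Sling Surgery access item can keep a look-back that reaches into pregnancy, because services can be used before birth.
2. At T2 and T3, ask all use items *Since you last completed these questions on [date]*, with the date filled in by Qualtrics. For a woman who skipped T2, the T3 item then covers the whole time since T1.
3. Re-express the whole-period options (*Once or twice*, *A few times*) so that they keep their meaning when the interval differs, for example as frequencies per week.
4. Record the completion date of every questionnaire.
5. Report the hire date from the Sling Surgery record beside the T2 use category for intervention women. A use rate per day in possession is not needed and could not be computed from these categories.

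The cost is a rewording of stems and some options, a piped date, and linkage of one date from the hire record. On-time T2 and T3 answers keep the same six-week reference period. The downside is longer and more variable recall for women who answer late or skip T2.

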## Aims and Hypotheses

A feasibility study is underpowered to reliably assess treatment effectiveness (Williams, 2016). Therefore the primary focus of a feasibility study is not hypothesis testing, though statistical analysis of between-group outcome differences may be conducted in a preliminary way in order to inform the sample size calculations of future RCTs (Williams, 2016). Instead, as a feasibility study, the focus of this study is on collecting information that will support the design of future studies, e.g. recruitment rates, treatment adherence etc.

The primary aim of this study is therefore to examine whether it is possible to conduct an RCT with this population (mothers of new-born infants) and intervention (sling use, training and support). This study has a particular focus around the feasibility of recruitment of this population and also around treatment fidelity, including whether control group participants independently engage in sling use during the trial.

While this study is underpowered to draw definitive conclusions around treatment effectiveness, it is predicted that sling use will lead to lower Postnatal Depression scores (as measured by the Edinburgh Postnatal Depression Scale (Cox, Holden, & Sagovsky, 1987), and higher wellbeing scores (as measured by the Warwick Edinburgh Mental Wellbeing Scale (WEMWBS); Tennant et al., 2007), parenting self-efficacy and responsiveness (as measured by the Parenting Sense of Competency Scale (PSCS); Gibaud-Wallston & Wandersman, 1978; and Caregiving Experiences Questionnaire (CEQ); Brennan, George & Solomon, 2013), and breastfeeding frequency and duration, in the intervention group, compared to the control group. It is predicted that any improvement seen in the scores on these measures post-intervention, in comparison to pre-intervention scores, will be significantly greater for intervention group participants, than any improvement seen for control group participants.

A secondary hypothesis is that maternal attachment style (as measured by the Experiences in Close Relationships Scale-Short (ECR-S; Wei, Russell, Mallinckrodt & Vogel, 2007) might act as a moderator of the relationship between sling use and the scores on these various measures.

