### *Data Security and Management*

Data will be stored using Qualtrics. Using this programme, the data is password protected and only accessible by the research team. Identifiable data will need to be kept, as participants will need to be reminded to complete T2 and T3 measures via phone or email (whichever is their preferred method) at the correct times, and data analysis relies on matching participants' data from each time point.

Contact details, as well as information about each participant's sling hire and any other access to Sling Surgery services will be securely stored on both Qualtrics and the sling surgery myTurn hire system, which is also password protected and only accessible by Sling Surgery staff. This will allow the sling surgery to follow their standard practice and keep track of where and when slings have been hired out.

Only secure university or Sling Surgery email addresses will be used to contact participants and the sim card used to contact participants will be kept in a locked location only accessible by research team members.

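### The fidelity questionnaire has no answer for one to about five Sling Surgery contacts, or for sling use on several days a week, and omits a promised question on other sling support

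*Protocol*

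**What the plan says.** The Protocol's Aims and Hypotheses section names treatment fidelity as a particular focus of the feasibility aim, including "whether control group participants independently engage in sling use during the trial". The instrument is a self-designed questionnaire, listed under Primary Measures and printed in Appendix B.

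- **Access to the Sling Surgery.** With a 6-week recall window, the item asks "how often would you say that you have accessed the sling surgery services (either online, in person, or other". Its answers are none, "About once a week", about twice a week, more than three times a week, and daily. The partner item is the same with a not-applicable option added.
- **Sling use.** The answers are none, one or two uses, a few uses, "About once a day", two or three times a day, and more than three times a day.
- **Other support.** The Measures section says participants are asked "how often they have accessed the services of the Sling Surgery over the past 6 weeks, or any other sling-related support".
- **Planned contact.** The recruitment poster (Appendix A) asks mothers to come "for a one-off session where you will learn how to safely use a sling". Templates S.7 and S.8 in Appendix S ask intervention mothers to attend within two weeks of the baseline questionnaires if possible.
- **Use in analysis.** Proposed Analysis suggests two re-analyses. One drops controls who used a sling or accessed the Sling Surgery. The other drops intervention mothers who did not use their sling regularly, a term it leaves undefined.
- **Other records.** Under Data Security and Management, sling hire and "any other access to Sling Surgery services will be securely stored on both Qualtrics and the sling surgery myTurn hire system".

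**The concern.** The contact the study expects most often is one visit, and the access item has no answer for it. A mother with one visit must choose between an answer that denies it and one that implies about six. In the control arm the same gap falls on the split that the contamination re-analysis needs, which is any access against none.

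For sling use, a workable cut-off for regular use could well lie at a few days a week. The item collects nothing in that range, so the choice of cut-off would be forced by the answer options.

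Response options fix what data exist. A statistical analysis plan can define terms and choose sources, but it cannot restore gradations that were not asked for. In a feasibility study, adherence and contamination rates are among the main results handed to the next trial.

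**Working it through.** The Protocol states no figure to reproduce here. The check turns each answer option into an implied count over the recall window and reads off the gaps.

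**Inputs.** Recall window 6 weeks, or 6 × 7 = 42 days (Appendix B). Planned size 25 to 30 per arm (Sample Size). One planned session (Appendix A).

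**Access item.** Implied contacts = weekly rate × 6.

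- None: 0
- Once a week: 1 × 6 = 6
- Twice a week: 2 × 6 = 12
- More than three times a week: above 3 × 6 = 18
- Daily: 42

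Nothing matches 1 to about 5 contacts. Exactly three a week is also absent, which matters less. A single visit is off by 1 from the zero option and by 6 − 1 = 5 from the weekly option.

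The same questionnaire shows that low counts were foreseen: its sling-swap item offers once, twice and three times over the same 6 weeks.

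**Timing.** T2 follows baseline by 6 weeks, and the visit is requested within two weeks of baseline. It should therefore normally fall inside the T2 recall window.

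**Illustration from the questionnaire alone.** Assume every intervention mother attends exactly once and has no other contact, and that a share q ticks the zero option while the rest tick a non-zero one. Recorded access = n × (1 − q).

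- n = 25: 25 at q = 0; 12.5, so 12 or 13, at q = 0.5; 0 at q = 1
- n = 30: 30, 15 and 0

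The true figure is 25 of 25 or 30 of 30 throughout. The recorded rate can lie anywhere from 0% to 100%, depending only on which ill-fitting answer is chosen. The Protocol gives no basis for a value of q, so this is a bound and not a forecast.

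**Sling-use item.** Implied uses:

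- None: 0
- One or two uses: 1 to 2
- A few uses: no number given
- Once a day: 42
- Two or three times a day: 2 × 42 = 84 to 3 × 42 = 126
- More than three times a day: above 126

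At one use per day of use, 2 to 5 days a week is 2 × 6 = 12 to 5 × 6 = 30 uses. These lie between a few and 42. Weekly use, about 6, can be placed coarsely under a few.

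**Promised question.** Set against the Measures text, Appendix B contains items on sling use, pram use, Sling Surgery access, the three partner versions, and swaps. None asks about sling support from elsewhere.

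**The case against.** The strongest reply is that attendance does not depend on this item. Intervention mothers book their session, attenders sign in (Intervention), and hire and other access are to be stored on Qualtrics and myTurn. Appendix P also asks at T3 about the first visit and later contact. This stands for in-person visits and hire. It does not settle the rest: the item expressly covers online contact, nothing in the Protocol describes how that would enter a hire system, and myTurn would not show support from another provider.

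Second, Proposed Analysis names no data source, and choosing one is properly left to a statistical analysis plan. That is fair, and the absence of a named source is not itself the fault here. The fault is in the answer options.

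Third, the main analysis is by intention to treat, and the re-analyses are offered tentatively. That limits the stakes for the outcome comparison, but not for fidelity as a result in its own right.

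Several stronger readings are tempting but unsupported.

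- A reader might infer that control contamination as a whole will be misclassified. None-versus-any sling use is recorded, because zero and one or two uses are separate answers.
- A reader might infer that the intervention itself goes unrecorded. The visit is only one part of it, alongside free hire for the study and continuing support.
- A reader might object that the 6-week look-back at baseline reaches before the birth. Those weeks add no uses for this baby, and Measures says the period may be altered.
- That controls might skip an item worded about their own sling is conjecture, since a zero answer is available.

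**Conclusion.** The point holds in a bounded form. The access items have no valid answer for 1 to about 5 contacts in 6 weeks. The sling-use item cannot grade use on 2 to 5 days a week, about 12 to 30 uses. The announced question on other sling support is absent.

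The consequence is that the questionnaire alone cannot reliably classify three things: occasional or online contact (above all in controls), support from other providers, and the degree of adherence. It does not follow that attendance or any sling use will be lost.

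The conclusion rests on reading the answer options literally as rates over 42 days, on one use per day of use for the sling item, and on the booking, sign-in and hire records being kept as described. The view that a cut-off for regular use may fall in the ungraded range is a judgement, because the Protocol does not define the term.

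**What to change.** - **Access items (mother and partner):** add low counts between none and weekly, for example once, and two or three times, with wording that leaves no gap up to the weekly option.
- **Sling-use items (mother and partner):** add one or more options for use on several days a week, below daily.
- **Other support:** add the question that the Measures section announces.
- **In-person attendance:** use the myTurn attendance and hire records as the source, keeping the questionnaire for online and other contact. This is subject to consent and access permissions: the consent form is not available here, and myTurn is described as open only to Sling Surgery staff. The debrief sheet (Appendix V) says contact details are not linked to questionnaire answers and that the University destroys its copy after debriefing. Any linkage must therefore be agreed in advance.
- **Regular use:** define it before the data are seen, in the Protocol or the statistical analysis plan.

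The cost is minor re-editing of a self-designed draft questionnaire and one data extract. No established scale is altered.
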